We propose a ***cross-sectional*** study to evaluate this specific aim. Each participant will undergo a VIA or VILI with specimen collection for p16^INK4a^ and HR-HPV and colposcopy by a different clinician during a single clinic visit. The study clinician performing the colposcopy will be blinded to the results of the VIA or VILI. For women in the VILI arm, the colposcopy will be performed first in order to eliminate any interference with colposcopy interpretation from the iodine staining. Biopsy decisions will be made at the time of colposcopy, but deferred until after the VILI. Any woman with cervical lesions suspicious for dysplasia seen at the time of colposcopy will undergo biopsy. Colposcopy will be used as the reference standard for presence or absence of CIN2/3, with biopsy results being the final diagnosis when available. Women with a normal colposcopy without biopsy will be considered to have no disease.Specific Aims 1, 2, 2a and 2b)

We propose a **prospective cohort** study using a subset of women identified from the cross-sectional study in Specific Aims 1 and 2a to evaluate specific aim 2c during a one-year follow-up visit. We will recruit women for this follow-up study who participated in the pilot p16^INK4a^ ELISA study (Aim 2a) and had normal colposcopy or CIN1. In a single visit, each participant will undergo a VIA with specimen collection for p16^INK4a^ and HR-HPV followed by colposcopy and biopsy if needed.

We propose a ***case-control*** study to measure and compare the presence and quantity of HIV-1 RNA in the cervicovaginal specimens of women with biopsy-confirmed CIN2/3 (cases) and age-matched women without evidence of cervical disease as measured by negative VIA (controls). We will compute the odds ratio for HIV-1 detection and compare log transformed mean viral loads between cases and controls. (Specific Aim 3)

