- **Cervical specimens for HIV-1 RNA detection and quantification:** A study clinician will place 3 Sno-Strip™ wicks (Chauvin Pharmaceuticals Ltd., Essex, England) in the posterior fornix of the vagina and allowing the vaginal fluid to absorb to each strip. The vaginal fornix was chosen instead of the endocervix because vaginal Sno-Strips provide a more reproducible detection and quantification of HIV-1 RNA than endocervical Sno-Strips, especially in the presence of endocervical mucus and debris.^88^ We also want to avoid disruption of the post-procedure healing cervix. The Sno-Strips will be placed in NASBA buffer and processed by the on-site laboratory within 2 hours of collection. After this time they will be placed in the –80º freezer until transport to the ARI-UCSF Laboratory of Clinical Virology for viral load testing.
- **Vaginal specimens for yeast, bacterial vaginosis and trichomonas:** After cervical specimen collection is complete, the study clinician will use a cotton swab to collect any fluid or discharge from around the posterior fornix and vaginal walls and place it in a test tube with 2cc of normal saline. The clinician will read the specimen immediately after the study examination and discard it after recording the results.

**Visual Inspection with Acetic Acid:** After identification of the cervical anatomy, including the squamo-columnar junction, the clinician will apply 5% acetic acid. After one to two minutes, the clinician will examine the cervix again to interpret the results of the VIA.

VIA will be defined as negative if the following findings are present:

- circumferential identification of the squamo-columnar junction (SCJ)
- no aceto-white lesions or faint, ill-defined, bluish white lesions at the SCJ or aceto-white lesions far away from the SCJ

VIA will be defined as positive if the following findings are present:

- well-defined, opaque aceto-white lesions touching the SCJ or surrounding the external os
- large circumferential aceto-white lesions covering the external os,
- pre-existing condyloma or leukoplakia which turns intensely white after application of acetic acid

**Visual Inspection with Lugol’s Iodine:** After identification of the cervical anatomy, including the squamo-columnar junction, the clinician will apply Lugol’s Iodine. After staining is noted in the transformation zone, the clinician will examine the cervix again to interpret the results of the VILI.

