VILI will be defined as negative if the following findings are present:

- circumferential identification of the squamo-columnar junction (SCJ)
- complete iodine uptake around the SCJ and into the transformation zone

VILI will be defined as positive if the following findings are present:

- well-defined, iodine yellow areas within or immediately surrounding the SCJ
- patchy areas of missing iodine uptake in the transformation zone

In order to maintain strict blinding of study clinicians, the results of the VIA or VILI will not be shared with the participant until after the colposcopy has been performed. The study clinician performing the VIA or VILI will leave the room with the data collection form containing the test results before the second clinician enters the room to perform the colposcopy.

**Colposcopy and biopsy:** Colposcopy will take place by a second, blinded study clinician immediately after VIA or VILI. Colposcopic exam will be done in accordance with the International Federation for Cervical Pathology and Colposcopy (IFCPC) guidelines,^89^ and will include sequential evaluation using green filter, acetic acid and Lugol’s Iodine. Findings on colposcopy that are suggestive of a CIN2/3 or worse lesion will prompt a colposcopically-guided biopsy. A normal colposcopy will be considered a final result indicative of no disease. (What about CIN1?) *the hgcin should have gotten a biopsy. The clinician performing the colposcopy will be assisted by the study nurse, who will also be blinded to the results of the VIA. They will have access to the participant’s clinical record, but not to the VIA results. Colposcopy findings will be recorded on a separate data collection form. After the colposcopy findings have been recorded the results of both tests will be discussed with the participant, including implications for treatment and future screening.

Study visits (Appendix E)

Specific Aims 1, 2a, 2b and 3:

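### The protocol contradicts itself on whether colposcopy precedes VILI; if it does, VILI accuracy and the VIA–VILI comparison are open to bias

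*Protocol*

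**What the plan says.** **Order of the tests.** The protocol's Study Design section (Specific Aims 1, 2, 2a and 2b) states: "For women in the VILI arm, the colposcopy will be performed first in order to eliminate any interference with colposcopy interpretation", the interference meant being that of iodine. It continues: "Biopsy decisions will be made at the time of colposcopy, but deferred until after the VILI". The Colposcopy and biopsy paragraph under Study Procedures gives the opposite order, with no exception for the VILI arm: "Colposcopy will take place by a second, blinded study clinician immediately after VIA or VILI".

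**What is put on the cervix.** The same paragraph says that the colposcopic examination "will include sequential evaluation using green filter, acetic acid and Lugol’s Iodine". This applies to every participant. VILI is itself read on iodine uptake: "After staining is noted in the transformation zone, the clinician will examine the cervix again to interpret the results of the VILI".

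**Blinding.** Study Design blinds the colposcopist to the VIA or VILI result. Study Procedures adds that these results are withheld from the participant until colposcopy is done, and that "The study clinician performing the VIA or VILI will leave the room with the data collection form containing the test results" before the colposcopist comes in. The assisting nurse is blinded to the VIA result. Colposcopy findings go on their own form, and a different clinician does each test.

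**Use of the results.** Aim 1 estimates the accuracy of both VIA and VILI. The abstract, the first null hypothesis and the Specific Aim 1 analysis all call for a comparison between tests that includes VIA and VILI. The planned allocation is 900 women to each.

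**The concern.** Colposcopy, with biopsy where taken, is the reference standard. In a diagnostic accuracy study the index test should be read without knowledge of the reference result. A reader who knows that result tends to agree with it, which raises apparent sensitivity and specificity together. Under the Study Design order this exposure is possible for VILI and not for VIA, so type of test and position in the sequence cannot be separated. Randomising women to VIA or VILI does not remove the problem, because it arises after allocation. No later analysis could separate the two effects.

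A second problem is physical. If the colposcopist has already applied acetic acid and iodine, VILI is no longer read on a fresh cervix. That could hide or create areas of absent uptake.

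**Working it through.** The protocol gives no figure for this bias, so there is nothing to reproduce. The main check is to follow each order through the text.

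| | Study Design order (colposcopy, then VILI) | Colposcopy and biopsy order (VILI, then colposcopy) |
|---|---|---|
| Is the VILI reader shielded from the reference result? | No concrete step does this | Yes, colposcopy has not yet happened |
| Is the colposcopist shielded from the VILI result? | Yes, VILI has not yet happened | Yes, by the stated steps |
| Cervix when VILI is read | Already exposed to acetic acid and iodine | No iodine from colposcopy |
| Cervix when colposcopy is read | No iodine from VILI | Iodine from VILI present |
| Same order as the VIA arm? | No | Yes |

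The operational blinding steps (the index-test clinician leaving with the form, and results withheld until colposcopy is finished) have a purpose only when the index test comes first. They were not adapted for a VILI arm in which it comes second.

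**Illustration of size.** Inputs:
- true sensitivity 75% and specificity 80% for both tests (planning values, Sample Size Calculation, Specific Aim 1);
- CIN2/3 prevalence 7% (Statistical Analysis, Specific Aim 1);
- positive predictive value of a positive colposcopy for CIN2/3, 57% (Sample Size Calculation, Specific Aim 2);
- share *f* of VILI readings that simply follow the colposcopic impression: **assumed**, 10–30%.

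Step 1. Accuracy of the colposcopic impression against the final diagnosis. A normal colposcopy without biopsy counts as no disease, so its sensitivity is taken as 100%. For specificity:
- share of women with a positive colposcopy = 0.07 / 0.57 = 0.1228
- false positives = 0.1228 − 0.07 = 0.0528
- specificity = 1 − 0.0528 / 0.93 = 94.3%

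Step 2. Apparent VILI accuracy:
- sensitivity = 0.75 + *f* × (1.00 − 0.75)
- specificity = 0.80 + *f* × (0.943 − 0.80)

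| *f* (assumed) | Apparent sensitivity | Apparent specificity |
|---|---|---|
| 10% | 77.5% | 81.4% |
| 20% | 80.0% | 82.9% |
| 30% | 82.5% | 84.3% |

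Step 3. Scale. With 900 women per arm, 900 × 0.07 = 63 have CIN2/3 and 837 do not. The approximate 95% half-widths per arm are:
- sensitivity: 1.96 × √(0.75 × 0.25 / 63) = 10.7 points
- specificity: 1.96 × √(0.80 × 0.20 / 837) = 2.7 points

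A shift of 2.5–7.5 points in sensitivity is inside the sampling error. A shift of 1.4–4.3 points in specificity is comparable with it. Each woman has only one visual test, so the arms are compared here as two independent groups (two-sided 5%, normal approximation). If the tests are truly equal, the chance of a significant specificity difference in favour of VILI is about 11%, 33% and 63% for *f* = 10%, 20% and 30%. For sensitivity it is about 5%, 10% and 18%. With no such reading the chance in that direction would be 2.5%.

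None of this includes the effect of acetic acid and iodine left from colposcopy, for which the protocol gives no basis.

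**The case against.** Several safeguards exist:
- a different clinician does each test;
- colposcopy findings are recorded on a separate form;
- biopsy waits until after VILI, so no biopsy site is visible to the VILI reader;
- the text declares a general aim of keeping study clinicians strictly blinded;
- the discussion with the participant covers both results, which presupposes that both tests are done.

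The timetable also provides for SOPs and a study manual, where room procedure could be set out. These points stand and narrow the gap. They do not close it. Separate clinicians and separate forms do not bar access, the measures attached to the blinding aim withhold only VIA or VILI results, and an unseen manual cannot be credited. A manual would in any case have to depart from one of the two stated orders.

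Different sequences in the two arms are not in themselves an error. The order was chosen for a stated reason.

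Three stronger readings may tempt a reader, and the protocol does not support them.
- *That the VILI results are biased.* The text shows a missing safeguard under one of two stated orders. It does not say that the VILI reader attends colposcopy, sees the form or learns the biopsy decision.
- *That iodine within colposcopy defeats the reason for putting colposcopy first.* Iodine is listed last in the colposcopic sequence, so the green-filter and acetic-acid stages are still read on a cervix free of iodine. The difficulty passes to VILI, but the rationale survives.
- *That specificity would be inflated to 82–86%.* This follows from 0.80 + 0.20 × *f* and treats colposcopy as error-free. A reader who copies colposcopy also copies its false positives, and the protocol's own 57% gives the lower range of about 81.4–84.3%.

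**Conclusion.** The contradiction on order is plain and has to be resolved, because staff cannot follow both passages. Conditional on the Study Design order, VILI accuracy and the VIA–VILI comparison are open to bias: the VILI reader is not reliably shielded from the reference result, and VILI is read after acetic acid and iodine have been applied. Both problems affect one arm only. Under the other order the VILI reader is protected, and the iodine interference with colposcopy returns.

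Reading with knowledge of colposcopy would tend to inflate VILI accuracy; prior staining could act either way. The size cannot be derived from the protocol. The illustrative ranges rest on an assumed 10–30% of readings following colposcopy, on true values of 75% and 80% for both tests, and on the protocol's 7% prevalence and 57% predictive value. The matter is important because analysis cannot repair it afterwards.

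**What to change.** Reconcile the Study Design and the Colposcopy and biopsy sections to one VILI-arm sequence, and word the blinding steps for that sequence.

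- **If colposcopy stays first:** require that the VILI reader is out of the room during colposcopy, has no access to the colposcopy form or the biopsy decision, and records the VILI result before any result is discussed. State how the colposcopic Lugol's step is sequenced so that iodine is not already on the cervix when VILI is read.
- **If VILI comes first:** state how the interference of its iodine with colposcopy is dealt with, since that was the reason given for the other order.

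The choice of order is for the sponsor. The cost is procedural wording and matching staff instruction. The two clinicians needed are already planned, and no change in sample size follows.

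If women have already been examined, the report should state which order was used for them and whether the VILI reader was unaware of the colposcopy result.

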**OBJECTIVES:**

General:

We seek to establish the link between the presence, diagnosis and treatment of cervical dysplasia and HIV genital shedding. We also seek to establish the sensitivity and specificity of three resource-appropriate screening methods, VIA, VILI and p16^INK4a^ biomarker testing, for cervical dysplasia.

Specific (Aims):

**Aim 1:** **To calculate the sensitivity, specificity, and the positive and negative predictive values of visual inspection of the cervix after application of 3-5% acetic acid (VIA) and visual inspection with Lugol’s Iodine (VILI) for the diagnosis of cervical intraepithelial neoplasia grade 2 and grade 3 (CIN2/3) in HIV-infected women.** HIV-infected women enrolled in care at the FACES clinics in western Kenya will undergo VIA or VILI and colposcopy with directed biopsy as indicated. The colposcopy will be used as the reference standard, allowing for calculation of sensitivity, specificity, positive and negative predictive value of VIA and VILI.

Hypothesis 1: VIA and VILI will have test characteristics validating their use as a screening test for cervical dysplasia among HIV-infected women in resource-limited settings.

**Aim 2: To define the quantitative value of a biochemical assay for p16^INK4a^ that predicts cervical neoplasia with the greatest sensitivity and specificity among HIV-infected women using a receiving operating characteristic (ROC) curve.**

**Aim 2a: To compare the sensitivity and specificity of the p16^INK4a^ biochemical assay with that of HR-HPV testing.** HIV-infected women enrolled in care at the FACES clinics in western Kenya will undergo specimen testing for p16^INK4a^ and HR-HPV, followed by colposcopy with directed biopsy as indicated.

**Aim 2b: To calculate the sensitivity and specificity of the p16^INK4a^ biochemical assay for the detection of CIN2/3 using colposcopy as the gold standard.** HIV-infected women will have p16^INK4a^ specimens collected prior to colposcopy. Diagnosis for positive p16 will be based on the ROC curve cut-off determined in the pilot study, with colposcopy as the reference standard as above.

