| Will undergo LEEP for CIN2/3 at one of the FACES study clinics in Kisumu | Allows baseline specimen collection and ensures the quality and standard of the LEEP |
| Willing to remain abstinent from sexual activities for four weeks post-LEEP and for three days prior to each follow-up study visit | Reduces risk of post-LEEP bleeding and infection. Reduces potential semen contribution to genital HIV-1 viral load measurements. |
| Exclusion Criteria | Rationale |
| Pregnant | May increase false positive rate of VIA^75^ |
| Clinical evidence of cervical or pelvic infection:   - Muco-purulent discharge - Cervical friability - Cervical motion tenderness found on pelvic exam in symptomatic women | May increase false positive rate of VIA^75^ |
| Cervical cancer screening at FACES within past 12 months | May influence clinician interpretation of results |
| Prior or current history of cervical surgery, dysplasia or cervical cancer | May influence test characteristics of colposcopy and VIA |
| Unsatisfactory VIA | Woman would require alternative screening method (cytology, colposcopy or endocervical sampling) per WHO protocol^74^ |
| *Additional Criteria for Specific Aims 3 & 4:* |  |
| Laboratory evidence of cervical infection:   - NAAT for Gonorrhea or Chlamydia - Wet mount showing bacterial vaginosis, candida or trichomonas | Concomitant sexually transmitted infections can increase the risk of HIV-1 genital shedding |

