We will sequentially recruit and enroll eligible women for all specific aims. There will be three separate consent forms (Appendix A, B and L). Screening and informed consent for participation in the studies involving VIA or VILI, colposcopy and specimen collection (S.A. 1, 2 and 3) will take place in a private gynecologic exam room prior to pelvic exam. Because satisfactory visual exam or clinical evidence of cervical or pelvic infection will only become evident after exam, participant numbers will be assigned after VIA and colposcopy. Women who are unsure about enrollment and would like time to consider will be given an information sheet (Appendix C) and may return for enrollment at a later date. VIA in these women will be deferred until their next visit. Eligibility and informed consent for the post-LEEP genital shedding sub-study will take place at a clinical visit, prior to their LEEP procedure. Women will be given an information sheet specific to this part of the study, in addition to the normal clinical materials in use that explain the LEEP procedure (Appendix D).

Statistical Considerations and Sample Size Calculation

**Specific Aim 1:** To calculate a sensitivity of 75% with a confidence interval of 5% in both directions and a two-sided alpha of .05, we will need to complete sequential VIA and colposcopy in ***1800* women**.^83^

To determine a specificity of 80%, with a confidence interval of 5% in both directions and a two-sided alpha of .05, we calculate that we will need to examine 400 women. Because the scientific outcome of specificity is most important, we will use the estimate of 1,800 women (900 VIA and 900 VILI to account for laboratory and sampling error) to power our study.

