Data Storage: The study will be conducted within the existing clinic settings in the Nyanza Province. Data will be collected from the electronic medical record and on study-specific forms (Appendices F and G). Study data will be included as part of the patient’s medical file and maintained in locked file cabinets within the clinic. Data will be abstracted to computers by data entry clerks and managed by the assigned data manager at each site. Abstracted data will be labeled by unique study ID only. A file correlating study ID and medical file number will be kept in separate password-protected Excel computer file and accessible only to the core research team. Additionally, all study computers are password protected and kept in locked offices within the clinics.

Statistical Analysis:

Statistical analysis for all specific aims will be carried out using STATA and SPSS software.

**Specific Aim 1**: The goal of specific aim 1 is to calculate the sensitivity, specificity and predictive values of VIA and VILI for CIN2/3, with colposcopy as the gold standard. Colposcopy will be performed on every participant, regardless of screening result, to avoid verification bias.^92^ To calculate the sample size for this study, we assume that the prevalence of CIN2/3 among HIV-infected women at FACES will be 7%, as has been seen in the cervical cancer screening program at FACES.^78^ Sample size calculations will be based on prior estimates of VIA sensitivity, as these are more prevalent and therefore have more precision.

Sensitivity: Previous studies have shown that VIA has a sensitivity of 60-86%^39, 40, 91, 93-97^ for detection of CIN2/3 among healthy women, which is comparable to the sensitivity of cervical cytology and would be an acceptable test characteristic for this setting. In order to determine sensitivity, we will construct a 2 x 2 table, and divide the number of women with a true positive VIA result (i.e. those with disease diagnosed by colposcopy and VIA) by the number of true positive VIAs plus the number of false negative VIAs. Specificity: Specificity values for VIA range from 64 to 94% for the detection of CIN2/3.^39, 40, 91, 98, 99^ To determine specificity of VIA, we will divide the number of participants with true negative VIA (i.e. has no disease diagnosed colposcopically) by the number of true negative tests plus the number of false positive tests.

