**Specific Aims 2c:** To compare the rate of detecting CIN2/3 at one-year follow-up between women with normal or increased levels of p16^INK4a^ at baseline, we will use the Pearson’s chi-square test to investigate any significant differences in the proportions. Based on our sample size calculations, we aim to have 80 percent power with a two-sided alpha of 0.05. To compare the rates of developing CIN2/3 at one-year follow-up between women with persistently elevated p16^INK4a^ compared to those with only one elevated measurement, we will also use the Pearson’s chi-square test to look for statistically significant differences in proportions of CIN2/3 in the two groups.

**Specific Aim 3:** To compare the presence and magnitude of HIV-1 genital shedding between women with and without cervical dysplasia we will compute the odds ratio of HIV-1 detection in genital secretions with 95% confidence intervals. Multivariate analyses will be performed using logistic regression to control for demographic and clinical confounders. Potential confounders include WHO stage of HIV disease, CD4+ count, plasma HIV-1 viral load, opportunistic infections, previous STIs and current use of anti-retroviral therapy.

**Specific Aim 4:** The goal of specific aim 4 is to determine the magnitude and duration of increased HIV-1 genital shedding that occurs after treatment with LEEP. Observed time trends in log copies of genital HIV-1 RNA will initially be evaluated via exploratory analyses of longitudinal measures based on scatter plot smoothing methods. Results will allow us to assess possible nonlinearities in trends, as well as investigate differences in results between subgroups of interest. The subgroups we are looking at include participants on HAART and who have CD4+ counts below 200. Further analyses will focus on estimation of post-LEEP changes from baseline levels in log copies of HIV-1 RNA using linear mixed effects regression methods. The primary predictor will be time on study (measured in weeks post-treatment). Initial models will include separate coefficients for each week of observation post-treatment (2, 4, 6, 10 and 14). Hypothesis 2 will be addressed directly via tests constructed about these coefficients. We will also explore the effect on results of adjustment for selected covariates, including demographic characteristics and baseline descriptors of participant health status.

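### Aim 3 controls are defined by negative VIA, which contradicts the protocol's own colposcopy/biopsy standard, and the handling of age matching in the analysis is left open

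*Protocol*

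**What the plan says.** Study Design (Specific Aim 3) compares "women with biopsy-confirmed CIN2/3 (cases") with "age-matched women without evidence of cervical disease as measured by negative VIA (controls").

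Elsewhere disease status is fixed differently:

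- Aim 1 under Objectives treats VIA and VILI as the tests on trial: "The colposcopy will be used as the reference standard, allowing for calculation of sensitivity, specificity, positive and negative predictive value of VIA and VILI".
- The first paragraph of Study Design makes colposcopy the standard for presence or absence of CIN2/3, lets biopsy override it when there is one, and counts a normal colposcopy without biopsy as no disease.
- Statistical Analysis, Specific Aim 1, states: "Colposcopy will be performed on every participant, regardless of screening result, to avoid verification bias".
- The second null hypothesis contrasts women with and without CIN2/3. Aim 3 under Objectives speaks of normal examinations and no evidence of cervical disease. Neither mentions VIA.

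Each woman gets one visual test: "Each participant will undergo a VIA or VILI with specimen collection". The Aim 1 sample size gives "1,800 women (900 VIA and 900 VILI to account for laboratory and sampling error").

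Study visits says controls are matched once cases are known. Statistical Analysis, Specific Aim 3, then gives an odds ratio with a 95% confidence interval and adds: "Multivariate analyses will be performed using logistic regression to control for demographic and clinical confounders". The potential confounders it names are WHO stage, CD4+ count, plasma viral load, opportunistic infections, previous STIs and antiretroviral use.

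**The concern.** Cases are classified by the reference standard and controls by an index test whose accuracy in this population is what Aim 1 sets out to measure. Three consequences follow from the written rule:

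1. The case and control disease definitions are not mutually exclusive.
2. Women in the VILI arm have no VIA result, so that arm can supply cases but not controls.
3. Disease-free women with a positive VIA are removed from the controls, with no corresponding restriction on cases.

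At stake is whether the Aim 3 odds ratio answers the stated question, CIN2/3 against no CIN2/3.

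Separately, a design matched on age calls for an analysis that takes age into account, and the text does not commit to one.

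**Working it through.** **The plan's own figure.** The sample size section states 46 women per arm (50 to be enrolled) for a difference of about 25 points, 80% power and two-sided alpha 0.05. The planning control rate is not given. The unpooled formula for two independent proportions is n = (1.96 + 0.8416)² × [p1(1−p1) + p2(1−p2)] / d².

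- 81% v 55%, the first cited study: 7.849 × (0.1539 + 0.2475) / 0.0676 = 46.6
- 40% v 15%, an assumed 25-point pair: 7.849 × (0.2400 + 0.1275) / 0.0625 = 46.2

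So 46 is consistent with an unmatched two-group calculation. Other formulas and rates give other values, for example 52 for 42% v 17% with pooled variance.

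**Inputs for the control definition.** CIN2/3 prevalence is 7%, with VIA sensitivity 60–86% and specificity 64–94% (Statistical Analysis, Specific Aim 1). The planning values are 75% and 80% (sample size, Specific Aim 1), and the VIA arm has 900 women.

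**Overlap of the definitions.** Expected CIN2/3 in the VIA arm is 900 × 0.07 = 63.

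- VIA-negative at 75% sensitivity: 63 × 0.25 = 15.75, about 16
- At 86%: 63 × 0.14 = 8.8
- At 60%: 63 × 0.40 = 25.2

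These women meet both disease definitions as written.

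**Share of VIA-negative women with CIN2/3.** f = 0.07(1−Se) / [0.07(1−Se) + 0.93·Sp].

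| Se / Sp | f | Expected in 50 controls |
|---|---|---|
| 75% / 80% | 0.0175 / 0.7615 = 2.3% | 1.15 |
| 86% / 94% | 0.0098 / 0.8840 = 1.1% | 0.55 |
| 60% / 64% | 0.0280 / 0.6232 = 4.5% | 2.25 |

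**Cost in power.** Assume true detection of 42% v 17%. With f = 2.3% the control rate becomes 0.17 + 0.023 × 0.25 = 17.6%, and the difference falls from 25.0 to 24.4 points. Power at 50 per arm (pooled normal approximation) falls from 79.2% to 77.0%.

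**Women barred from the control group.** Of disease-free women given VIA, 6% to 36% (1 − Sp) are excluded as false positives, as are all 900 VILI women. Half of the expected cases (63 of 1,800 × 0.07 = 126) arise in the VILI arm. Supply is not the difficulty: even at 64% specificity, 900 × 0.93 × 0.64 = 536 disease-free VIA-negative women remain before the further Aim 3 criteria.

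**Matching.** Age matching appears in the design. The named confounders omit age, although the Predictor Variables section lists it among the demographic variables. Whether matching is individual or by frequency is not stated. A paired analysis of 50 pairs at 42% v 17% would have about 77% power at within-pair correlation 0 and 81% at 0.1 (McNemar normal approximation). The correlations are assumptions; the protocol gives none.

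**The case against.** **Contamination may be nil in practice.** The VIA misses counted above are women whom the study's own colposcopy and biopsy identify. By the time controls are matched they are known cases, and Aim 3 under Objectives already describes the comparison group as free of disease. A sensible team would not use them as controls. This stands, and it makes 1.1% to 4.5% an upper reading. It does not repair the rule, which still names VIA as the measure of disease-free status.

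**The VILI arm is not needed for numbers.** Only 50 controls are required, and the abstract describes VIA against VILI as randomised, so drawing controls from one arm is not in itself a bias. This stands. The abstract also speaks of a small subset rather than 900 and 900, so the size of the VILI arm is uncertain. On either reading a woman given VILI lacks the result that the rule requires.

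**Inflammation.** A reader might infer that VIA-negative controls are unusually uninflamed and that the odds ratio is therefore overstated. The Exclusion Criteria do give "May increase false positive rate of VIA" as a reason concerning infection, and the Background links cervical inflammatory markers to HIV-1 in secretions. But that reason is given for excluding clinical infection, and Aims 3 and 4 also exclude laboratory-detected infection, in cases and controls alike. Nothing in the protocol says that VIA-positive, infection-free, disease-free women shed more virus. Residual selection is possible; its size cannot be calculated, and an overstated odds ratio is not established.

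**Matching.** A reader might infer that the matched data will certainly be analysed without age and that the odds ratio will be diluted by a stated amount. The text does not support that. Demographic confounders are to be controlled, the named list is not exhaustive, age is a listed predictor and pair matching is never stated. Any figure for the dilution would need an age effect that the protocol does not give. What stands is narrower: the design fixes age as a matching factor and the analysis text does not commit to using it.

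**Conclusion.** The inconsistency is real and lies in the definition of who is a control, which belongs in the protocol. The VIA rule conflicts with the protocol's reference standard and with the Aim 3 question. It lets about 16 women (9 to 25 over the quoted sensitivities) satisfy both disease definitions, makes VILI women eligible on one side only, and selects controls but not cases on VIA.

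The numerical consequence that can be calculated is small: about 1 of 50 controls and roughly 2 points of power, or close to nothing if known cases are kept out. These figures rest on 7% prevalence, the VIA accuracy quoted by the protocol, 900 women given VIA, and for power an assumed 42% v 17%. No net direction of bias in the odds ratio can be claimed. The age-matching point is a gap in commitment rather than a demonstrated error. The correction is worth making because it is nearly free.

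**What to change.** 1. In Study Design (Specific Aim 3), replace negative VIA by the reference standard: controls are women with a normal colposcopy or, if the null hypothesis is the intended contrast, women without CIN2/3 on colposcopy/biopsy. The two differ in whether women with CIN1 may be controls, so choose one and align the null hypothesis, Aim 3 under Objectives and Study Design with it.
2. Allow controls from either visual-test arm and state that no woman may be both case and control.
3. In Statistical Analysis, Specific Aim 3, say whether age matching is individual or by frequency. State that age is always in the logistic model, or use conditional logistic regression on the matched sets if matching is in individual pairs.

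The cost is wording only. Every participant already has colposcopy, and the HIV-1 specimens are collected at the enrolment visit and frozen until cases are identified, so no extra visit or test is needed.
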